| Methodology / Study Design | 
Interventional Biomedical research with bodily fluid samples obtained from healthy volunteers. Monocentric study, using recruitment that will be regional, prospective, randomized and controlled.
 
Twelve teams will be randomized into two equal groups, 1 and 2. Each team will be composed of 4 persons (1 senior physician, 1 resident, 1 nurse, 1 ambulance driver), all of whom will have received in advance the same theoretical and practical education as concerns IO access. Group 1 will undergo 9 simulations in 12 months whereas group 2, only 3.
                                                                                                                                                                                                                                                                                                                                                                                                                                                                                                                                                                                                                                                                                                                                                                                                                                                                                                                                                                                                                                                                                                                                                                                                                                                                                                     |

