#### **4.3.4.Supervisors and evaluation**

Two independent supervisors at a time will evaluate each simulation session of the Sim-Stress research protocol.

These supervisors, who are members of the University Hospital of Poitiers

(CHU de Poitiers) Simulation Laboratory, will be chosen in random manner. They each have different specialities, and are all simulation trainers, qualified in performing debriefing sessions.

This team of supervisors will consist of [name] (pediatric intensivist), [name] (pediatric emergency physician), [name] (surgical intensivist), [name] (adult emergency physician), and 4 emergency or pediatric fellows. They will analyze global performance with the respect to algorithm, IO access performance and global teamwork - leadership and communication. The mean between the two supervisors' scores will be used as the reference value. Interobserver reproducibility will be calculated according to the scale used.

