### **7.2. Description of the parameters involved in the evaluation of stress**

Parameters involved in the *evaluation of stress* will be estimated for every participant, and are described in paragraph 4.2.1

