##### **9.1.2.Evaluation of the effect of stress on performance**

The relationship between

- The various variables and indicators of stress (salivary cortisol concentration, Holter parameters of, scores from the various stress scales) evaluated during the 1-st session (basal stress) and during the following sessions,
- And performance (global performance, IO insertion and teamwork evaluation scores), evaluated during the latter sessions,

will be studied by calculating a Pearson correlation coefficient (or Spearman correlation coefficient if need be). This calculation will be realized on the entire study population as well as within each of the groups 1 and 2. A search for any sort of heterogeneity based on status (senior physician, junior physician, nurse, ambulance driver) will be undertaken, as well.

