##### **9.1.6.Inter-observer reproducibility**

### **9.2. Number of participants to be included in this study and statistical justification**

The necessary number of participants was calculated to answer the main objective of the study: determine if there is relationship between stress and performance.

To determine if there is a relationship between stress and performance, such that the correlation coefficient will attain a value of at least 0,50, with type I error at 5 % and power at approximately 90%, using a bilateral test, the number of subjects to be included is calculated to be 48 (Proc POWER, SIEVE). Our study will include 12 teams of 4 persons each, and each team will include representatives from four status categories (a senior physician, a junior physician (resident ["interne"]), a nurse and an ambulance driver.

To answer secondary objectives, the teams will be distributed in 2 randomised groups, 1 and 2.

It is noteworthy that in a previous study, a sample size of 12 participants each of the professional categories allowed for finding a difference of 2,1 points on an IO access evaluation scale of 20 points (Oriot 2012), knowing that the standard deviation of this score was described to be 1,02 in a previous study.

On the other hand, there is lack of sufficient information in the literature with regard to the number of subjects necessary to determine if there is a difference in the variability of various scores. The power of our study for questions corresponding to secondary objectives will thus be calculated *a posteriori* from the data actually observed.

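### The pooled stress–performance correlation in 9.1.2 has no status term, so differences in stress between professions can only dilute it; a minor refinement, to be made together with team-level inference

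*Protocol*

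**What the plan says.** Section 9.1.2 studies the relation between stress indicators and performance scores with a Pearson coefficient, or Spearman if needed. On the population it says "This calculation will be realized on the entire study population as well as within each of the groups 1 and 2". No covariate or stratum enters that coefficient. Status appears in the next sentence as a further step, "A search for any sort of heterogeneity based on status", with no method given.

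Section 9.2 sizes the study on this relation. It sets the target in these words: "such that the correlation coefficient will attain a value of at least 0,50". The test is two-sided at 5%, with power of about 90%. The outcome of the calculation is that "the number of subjects to be included is calculated to be 48 (Proc POWER, SIEVE").

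Three design facts bear on it:
- The protocol summary (methodology) fixes team composition: "Each team will be composed of 4 persons (1 senior physician, 1 resident, 1 nurse, 1 ambulance driver").
- Section 7.2 says that stress parameters "will be estimated for every participant".
- Section 4.2.1 places all the performance scales under team performance, and 4.3.4 reduces the two observers' ratings to one figure: "The mean between the two supervisors' scores will be used as the reference value".

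Stress is thus an individual measurement, and performance is one score per scale per team session.

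**The concern.** The four members of a team carry four stress values and one shared performance score, and each profession is represented once in every team. Profession is therefore exactly balanced against performance. If leaders are on average more stressed than drivers, that difference widens the spread of the stress variable but cannot line up with high- or low-performing teams. It enlarges the denominator of r and leaves the numerator alone.

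The protocol gives some reason to expect such differences. Training requirements differ by status (5.1), and stress-management strategies are studied only in the senior physician (4.2.2, 7.1).

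At stake is the coefficient on which 9.2 bases the sample size. If the relation of interest is the one within a profession, the pooled coefficient understates it.

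**Working it through.** **1. The protocol's own figure.** Inputs from 9.2: r = 0.50, two-sided 5%, power about 90%. By Fisher z, with atanh(0.50) = 0.5493:

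N = ((1.960 + 1.282) / 0.5493)² + 3 = 37.8, so 38.

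The stated 48 is not reproduced. At N = 48 these inputs give 96% power. The difference is on the safe side and matters here only as a margin: 48 independent pairs leave some room before power falls below 90%.

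**2. The dilution.** Write each stress value as a status mean plus a remainder. In a complete layout of 12 teams × 4 statuses with a score shared within team, the covariance between status means and performance is exactly zero. The covariance with total stress is therefore the covariance with the remainder alone, while the stress variance is larger by a factor 1/(1 − η²). Hence

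pooled r = status-adjusted r × √(1 − η²).

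On a simulated 12 × 4 data set, adding profession shifts raised η² from 0.06 to 0.73. Pooled r fell from 0.71 to 0.38 while the status-centred r stayed at 0.73, and both pooled values match the formula. The identity is exact for Pearson with complete data. It is approximate for Spearman or with missing individual values.

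**3. Size, if 0.50 is the within-status correlation.** The documents give no η², so it is assumed over a range. Power uses Fisher z on the protocol's basis of independent pairs: 48 for the whole population, 24 for each group.

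| η² (assumed) | pooled r = 0.50 × √(1 − η²) | power, 48 pairs | N for 90% | power, 24 pairs |
|---|---|---|---|---|
| 0 | 0.50 | 96% | 38 | 71% |
| 0.1 | 0.47 | 93% | 43 | 66% |
| 0.19 | 0.45 | 90% | 48 | 60% |
| 0.2 | 0.45 | 90% | 49 | 60% |
| 0.3 | 0.42 | 85% | 56 | 53% |
| 0.4 | 0.39 | 78% | 66 | 47% |

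The protocol claims no power for the by-group coefficients; the last column only shows that they have no margin.

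**4. Size, if 0.50 is the pooled correlation.** Any dilution is already inside the target, and there is no loss against it.

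**5. Whether adjusting for status is enough.** Simulation under no relation, 12 teams × 4 statuses, nominal two-sided 5%. The within-team correlation of stress (ICC, after removing status) is assumed.

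| ICC | η² | pooled r on 48 values | status-partial r on 48 values | team-mean stress against team score, 12 pairs |
|---|---|---|---|---|
| 0 | 0.2 | 3% | 5% | 5% |
| 0 | 0.4 | 1% | 5% | 5% |
| 0.3 | 0.2 | 11% | 15–16% | 5% |
| 0.3 | 0.4 | 6–7% | 15–16% | 5% |
| 0.4 | 0.2 | 14% | 19% | 5% |
| 0.4 | 0.4 | 9% | 19% | 5% |

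When teammates' stress is unrelated, the pooled test is conservative. When it is correlated, 48 values sharing 12 scores are not 48 independent pairs. Removing the status noise then exposes that error, which the noise had partly hidden. Only the team-level analysis keeps its level throughout.

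**The case against.** **Status is not ignored.** A reader might infer that the protocol disregards profession. It does not: the heterogeneity search follows directly in 9.1.2, and if carried out as status-specific correlations it would be free of between-profession variance. That stands. The search nevertheless sits beside the pooled coefficient and leaves it unchanged.

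**0.50 may be the pooled value.** Section 9.2 attaches 0.50 to a correlation without qualification, and 9.1.2 computes it pooled. A marginal and a status-adjusted correlation are different quantities, and choosing the first is not an error. This stands too. It follows that bias and loss of power cannot be asserted outright, only conditionally on the within-status reading.

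**The stated power survives over part of the range.** It does, up to η² of about 0.19, and nothing in the documents shows that η² is larger. A reader might conclude from the table that the study is underpowered on this account; the documents do not support that.

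**The power figures use a basis that the argument undermines.** This is correct. They show the effect of status with the protocol's other assumptions left in place. They are not the study's actual power.

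**Mixed models are mentioned.** Section 9.1.3 envisages them as a possibility for score changes over sessions. They are not committed to and do not replace the coefficient in 9.1.2.

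**Conclusion.** The point holds in a limited form. The whole-population and by-group coefficients in 9.1.2 contain no status term, and in this balanced design profession differences in stress can only pull a Pearson coefficient towards zero. If 0.50 is a within-status value, the pooled r is 0.47 to 0.39 for η² of 0.1 to 0.4, with power of 93% to 78% on 48 independent pairs. If 0.50 is the pooled value, there is no loss. The size rests on an assumed η² and on complete data.

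A reader might also infer that a status-partial correlation on the 48 values would settle the matter. It would not: at an assumed ICC of 0.3 to 0.4 its type I error is about 15% to 19%, higher than that of the unadjusted coefficient at the same η². The sharing of 12 team scores among 48 people is the larger problem.

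This is a minor refinement, best merged with the correction for clustering by team.

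**What to change.** - **9.1.2:** estimate the whole-population and by-group relation with status accounted for and the team as the independent unit. Either fit a model with status as a fixed effect and team-level inference (a team random effect or equivalent), or correlate team-mean stress with the team score. With complete data every team mean averages the same four statuses, so status cancels; if individual values are missing, centre stress within status before averaging. Do not apply a status-partial correlation to 48 values as though they were independent.
- **9.2:** state whether 0.50 refers to the pooled or the status-adjusted correlation. If team means are used, restate the target for them, because a team-mean coefficient is a different quantity from an individual one.
- **Heterogeneity by status:** keep it as a separate exploratory step.

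Cost: a few sentences and a few degrees of freedom (3 for status). Status is already recorded and no new data are needed. The real downside is that stated precision will look less favourable once the team is the unit: 12 independent pairs at r = 0.50 give about 38% power by the same Fisher z method. That reflects the design and is not created by the adjustment.

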##### **9.1.3.Evaluation of performance score variations**

Variations in global team, IO access, and teamwork performance scores will be estimated in terms of temporal sequence. In each of the groups 1 (9 sessions) and 2 (3 session), score modifications between the various simulation sessions will be tested by means of an ANOVA for repeated measures (or the Friedman non parametric test, if need be).

Concerning the entire study population, linear mixed effects models (for continuous responses observed over time) will eventually be used envisaged so as to take into account, in a common analysis, the entire set of data collected throughout the various sessions, and, more notably, parameters involved in the development of stress management strategies compared to stress and repeated simulations.

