##### 4.4.2.2. Number of team simulation sessions:

Participants of group 1: 6 teams x 9 sessions = 54 simulation sessions

Participants of group 2: 6 teams x 3 sessions = 18 simulation sessions

TOTAL = 54 + 18 = 72 team stimulation sessions

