### **6.2. Evaluation of the effect of repeated simulation sessions**

Next, we shall estimate the effect of **repeated simulation sessions** on a team's **performance evolution** in terms of safety preservation as concerns an infant in a state of shock, using three parts:

- By estimating the impact of repeated simulation sessions on global team performance (determined by degree of respect for the appropriate algorithm);

University Hospital of Poitiers - CHU de Poitiers Sim-Stress

- By estimating the impact of repeated simulation sessions on insertion of an IO access: insertion technique (evaluation scale), decision-making timing and duration;
- By estimating the impact of repeated simulation sessions on teamwork: evaluation of leadership (evaluation scale) and communication (evaluation scale).

Finally, we shall study the effect of the *repeated simulation sessions* on stress by evaluating various stress markers (biological, electrophysiological and psychological), as well as its impact on stress management strategies. We shall so be able to determine if *simulation session repetition*, expected to improve performance, will be accompanied by high stress levels following implementation of stress management strategies, or if it will be accompanied by a decrease in stress levels. Evaluation of the effect of the *repeated simulation session* will be evaluated by comparison of the 2 groups, i.e. the teams that will participate 9 vs. 3 simulation sessions, as described in paragraph 9

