### **9.3. Degree of statistical significance**

A *p* score < 0.05 will be considered as statistically significant

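### Section 9.1.3 asks how performance evolves over successive sessions, but the only within-group tests it commits to ignore session order

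*Protocol*

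**What the plan says.** Section 9.1.3 opens with its aim: "Variations in global team, IO access, and teamwork performance scores will be estimated in terms of temporal sequence". For each group separately it then commits to a test: score changes between sessions "will be tested by means of an ANOVA for repeated measures (or the Friedman non parametric test, if need be"). It names no trend contrast, ordered alternative or session-number term for these tests.

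The next paragraph of 9.1.3 says that, for the whole study population, "linear mixed effects models (for continuous responses observed over time) will eventually be used envisaged". It does not say how time would enter the model.

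Section 6.2 frames the question as one of performance evolution, with repetition "expected to improve performance". Section 4.4.2.2 gives the sizes: "6 teams x 9 sessions = 54 simulation sessions" in group 1 and "6 teams x 3 sessions = 18 simulation sessions" in group 2. Section 9.3 sets the level: a p "score < 0.05 will be considered as statistically significant".

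**The concern.** The aim concerns order: whether scores move in a direction as sessions accumulate. The null of the committed tests is that no session differs from any other. Shuffling the session labels changes neither statistic, so a significant result is not in itself evidence of learning.

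The F test's level also depends on sphericity, which group 1 is too small to check. At stake is the within-group statement about learning in the 9-session group. The test behind it may reject without any trend, may have the wrong level, and under some plausible patterns has less power than a test that uses the order.

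**Working it through.** **Inputs.** From the protocol: 6 teams per group, 9 or 3 sessions (4.4.2.2), alpha 0.05 (9.3). The protocol gives no power figure, correlation, within-team SD or learning curve for these tests, so there is no stated figure to reproduce. Its sample size of 48 (9.2) concerns a correlation and does not bear on this point. Assumptions: normal scores, total SD = 1, and either compound symmetry with ρ = 0.5 or AR(1) correlation between sessions. Tests are two-sided at 5%.

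**Order invariance.** For one simulated 6 × 9 data set, permuting the sessions left both statistics unchanged (F = 1.709, Friedman 10.84).

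**Sphericity.** The sample covariance from 6 teams has rank at most 6 − 1 = 5. Nine sessions have 9 − 1 = 8 within-team contrasts. As 5 < 8, neither a sphericity test nor the multivariate version of the analysis can be computed.

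**Level with no change at all** (simulation, at least 20,000 data sets per case):

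| Correlation | Uncorrected F | Epsilon-corrected F | Slope test |
|---|---|---|---|
| Compound symmetry 0.5 | 5.0% | 0.6% | 5% |
| AR(1) 0.5 | 7.5% | about 1.5% | 5% |
| AR(1) 0.8 | 11.0% | 2.8% | 5% |
| AR(1) 0.9 | 12.1% | about 3.4% | 5% |

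The slope test fits each team's least-squares slope on session number and applies a one-sample t test on 5 df. It needs no sphericity.

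**Power, group 1, compound symmetry 0.5.** With session means μ_j and centred session numbers c_j = −4, …, 4 (Σc_j² = 60):

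- ANOVA: noncentral F on 8 and 40 df, λ = 6 Σ(μ_j − μ̄)² / (1 − ρ).
- Slope test: noncentral F on 1 and 5 df, λ = 6 (Σ c_j μ_j)² / [60 (1 − ρ)].

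For a linear rise D from session 1 to 9, Σ(μ_j − μ̄)² = D² × 60/64 = 0.9375 D², and the two λ are equal. D = 1.0 gives 6 × 0.9375 / 0.5 = 11.25; D = 0.8 gives 7.2.

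| Linear rise (total SD) | ANOVA | Slope test | Gap (points) |
|---|---|---|---|
| 0.5 | 15% | 28% | 13 |
| 0.8 | 36% | 58% | 22 |
| 1.0 | 55% | 76% | 21 |
| 1.25 | 79% | 91% | about 13 |
| 1.5 | 93% | 98% | 5 |

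Simulation agrees. For a 1.0 SD rise it gives Friedman 43% and the epsilon-corrected F 23%.

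**One odd session.** If all six teams score 1 SD lower in session 5 only, Σ(μ_j − μ̄)² = 1 − 1/9 = 0.889 and λ = 6 × 0.889 / 0.5 = 10.67. ANOVA rejects 53% of the time. The slope test rejects 5%, because session 5 is the midpoint (c_5 = 0). An odd session at either end does move the slope: λ = 6 × 16 / (60 × 0.5) = 3.2, and the slope test rejects 31%.

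**Jump then plateau.** A 1 SD rise after session 1 that then holds has the same two λ, 10.67 and 3.2: ANOVA 53%, slope test 31%. So ANOVA has the same rejection rate for a lasting early gain as for one bad session in the middle. This pattern also favours ANOVA over the slope test.

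**Serial correlation, linear rise 1.5 SD.** AR(1) 0.5: uncorrected F 64%, corrected 36%, slope 57%. AR(1) 0.7: 70%, 43%, 54%. The slope test gains over the corrected F only; the uncorrected F is ahead, but at an inflated level.

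**Group 2.** With c = −1, 0, 1 the slope is (session 3 − session 1)/2, so session 2 drops out. For a linear rise of 1.0 SD, ANOVA on 2 and 10 df has 45% and the slope test about 51%. With a plateau after session 1 the order reverses, 57% against about 51%.

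**The case against.** The omnibus tests fit the sentence that names them, since "score modifications between the various simulation sessions will be tested by means of an ANOVA for repeated measures". If one session truly differs, rejecting that null is correct. The effect of repetition is to be judged by comparing the groups (6.2), through the ordered first-to-final change in 9.1.4, so 9.1.3 is supporting work for a secondary objective. The mixed-model sentence shows that time was considered, and contrasts or epsilon corrections are often left to an SAP.

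Much of this stands. The omnibus test is not invalid for its own null, and the point is of secondary weight. However, the mixed model is tentative, pooled over both groups and has no stated time term, and 9.1.4 compares groups on two time points. Neither supplies a within-group account of sequence, which is the aim 9.1.3 sets itself. The objection is to the test the protocol names, not to detail it omits.

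A reader might infer two stronger things. One is that ANOVA costs 20 or more points of power in general. It does not: the figure needs a moderate, steady rise with exchangeable errors, and the protocol supplies neither a correlation nor a learning curve. The other is that the slope test should replace ANOVA. The jump-and-plateau result argues against that, and the expected result in the protocol summary, that high performance is maintained, fits a plateau as well as a steady climb.

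The odd-session example assumes a shift shared by all six teams in the same session. Scenarios are drawn by lot (4.3.2), and the protocol does not say whether teams share a scenario at a given session.

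**Conclusion.** The concern holds in a limited form. Section 9.1.3 sets a question about order and commits only to order-free tests. That, and the impossibility of checking sphericity with 6 teams and 9 sessions, follow from the design and rest on no assumed effect.

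The sizes do rest on assumptions. The uncorrected F rejects about 7 to 12% under a null with AR(1) correlation 0.5 to 0.9. The power deficit is about 20 points in group 1 for a steady rise of 0.8 to 1.0 total SD under compound symmetry 0.5. It is smaller for smaller or larger rises, absent against the uncorrected F under serial correlation, about 5 points in group 2, and reversed for an early jump then plateau. This supports adding a trend analysis, not discarding the omnibus test.

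**What to change.** In 9.1.3, for group 1, pre-specify a one-df session trend as the test of evolution: fit each team's slope on session number (1 to 9), test the mean slope with a one-sample t on 5 df, and report it with its 95% CI. Keep the repeated-measures ANOVA or Friedman as the test of any between-session difference, and state that its significance is not by itself evidence of learning. For group 2, report the change from session 1 to session 3 with its CI beside the existing test.

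The cost is protocol or SAP wording and a few lines of code, with no new data. It adds one pre-specified analysis. The linear trend is less sensitive to an early jump followed by a plateau, which the retained omnibus test covers.
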